#### Performance of Outcome Measures

To define the performance of the CVSS and the performance of the three psychophysical visual processing tasks, the standard deviation and test-retest reliability for CVSS and each of the three psychophysical tasks will be determined. The CVSS and the three psychophysical tasks will be given pre-treatment and then repeated on the 1st day of treatment prior to rTMS, and these results will be used to conclude the test-retest reliability using the intraclass correlation coefficient (with a two-way mixed effects, absolute agreement, single rater/measurement model).

#### Outcome Measure Changes With Treatment

Changes in outcome measures (i.e., changes in the CVSS, VFQ-25, and GAD-7) with treatment will be assessed. Results pre-treatment (first day of treatment prior to rTMS) and results after last day of treatment with rTMS will be compared by assessing within-subject correlations (i.e., repeated measures correlation) for the CVSS, VFQ-25, GAD-7, and the suppression index (center-surround task), detection threshold (luminance detection task), and coherence threshold (global motion task). The effect size for each measure using a linear mixed model will be determined.

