**Criteria A through D must be met**
A. Dynamic, continuous tiny dots in the entire visual field >3 months
B. At least two of four additional symptoms 1. Palinopsia (visual after-images, trailing of moving objects, or both) 2. Enhanced entoptic phenomena with at least one of the following: excessive floaters in both eyes, excessive blue field entoptic phenomenon, self-lighting perceived with eyes closed, or spontaneous photopsia. 3. Photophobia 4. Nyctalopia
C. Symptoms not consistent with typical migraine visual aura per International Headache Society criteria.
D. Symptoms are not better explained by another disorder (including normal ophthalmic tests and no intake of psychotropic drugs).

The objective of this manuscript is to describe the research protocol for an ongoing, open-label treatment study of repetitive transcranial magnetic stimulation (rTMS) for VS syndrome at the University of Colorado School of Medicine. The aim of this pilot study is to investigate the feasibility of a future randomized controlled trial of rTMS to improve visual function and symptoms associated with VS. Specifically, this study aims to determine: (1) adverse events and drop-out rate, (2) the standard deviation and test-retest reliability of a novel scale (Colorado Visual Snow Scale or CVSS) and performance of three psychophysical visual processing tasks previously investigated by McKendrick et al., and (3) describe changes in outcome measures (described below) following treatment with rTMS.

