## Methods and Analysis

The ongoing study is an open-label feasibility treatment study of VS utilizing a rTMS paradigm. In summary, participants undergo a 2-week treatment intervention for a total of 10 sessions that are ~1 h in duration per session and occur 5 days per week for two consecutive weeks. Assessments described are given at baseline (pre-treatment), post-treatment, and again at 1 and 3 months following treatment.

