### Description of Population Being Enrolled

Up to 10 participants ranging in age from 19 to 65 with a diagnosis of VS that meets the International Headache Society (IHS) criteria are being recruited.

Inclusion Criteria:

Age 19–65 years with a diagnosis of VS that meets IHS criteriaAble to provide informed consentVisual snow must be present for 3 months or more and symptoms must be persistent (i.e., continuous)A prior brain magnetic resonance imaging (MRI) scan with and without contrast completed in the past 3 years that does not show signs of clinically significant brain lesion(s) (e.g., no evidence of multiple sclerosis, stroke, brain tumor, cortical heterotopia or other cortical developmental abnormalities, arteriovenous malformation, etc.).

Exclusion Criteria based on TMS safety guidelines (14–16):

Syndrome meeting criteria for Hallucinogen-persisting perception disorderPrior treatment with TMS for any disorderEpilepsy, family history of epilepsy, or personal history of seizuresAny medical condition or medication that increases the risk of seizuresPacemaker or another implantable medical deviceMetal in the skull, not including the mouthUnstable cardiac, pulmonary, or other systemic illnessPregnancyBipolar disorderHistory of suicidality.

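### The pre/post comparison is assigned to a repeated measures correlation with no named pair of variables, and on no reading does it give the amount of change

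*Protocol article*

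**What the plan says.** Aim (3) in the Introduction of the protocol article is to "describe changes in outcome measures (described below) following treatment with rTMS". The matching analysis is in Data Analysis, under Outcome Measure Changes With Treatment. It has three parts:

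- The purpose: "Changes in outcome measures (i.e., changes in the CVSS, VFQ-25, and GAD-7) with treatment will be assessed".
- The comparison: "Results pre-treatment (first day of treatment prior to rTMS) and results after last day of treatment with rTMS" are the two occasions, and they "will be compared by assessing within-subject correlations (i.e., repeated measures correlation) for the CVSS, VFQ-25, GAD-7". The sentence goes on to the suppression index, the luminance detection threshold and the motion coherence threshold, so six measures are covered.
- A further analysis: "The effect size for each measure using a linear mixed model will be determined".

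The section does not name the two variables that enter each correlation. It does not say whether the effect size is in raw or standardised units.

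**The concern.** A section about change compares the two occasions with a measure of association. A correlation coefficient has no units and is bounded by 1, so it cannot tell a reader how many points a scale moved. The pair of variables is also left open, so two analysts could follow the sentence faithfully and report different quantities under the same heading.

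The study is meant to inform a future randomised trial. Planning that trial requires the mean change on each measure, its uncertainty and a defined SD. If the correlation is reported as the pre/post result, none of these follows from it. On one reading, a coefficient that looks like a treatment finding can arise from measures that merely drift over the same period.

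**Working it through.** **Inputs.** From the article: n up to 10 ("Up to 10 participants ranging in age from 19 to 65"), one arm, and two occasions in the comparison. The section states no SD, pre/post correlation, expected change or precision for this analysis, so there is no figure to reproduce. Every SD and mean change below is an illustrative assumption.

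**Reading 1: pre against post of the same measure.** With N participants and k pairs each, a repeated measures correlation has N(k - 1) - 1 degrees of freedom. Here each participant supplies one pre/post pair, so k = 1 and df = 10 × 0 - 1 = -1. It cannot be estimated. An ordinary correlation across participants can be computed, but it is a different method and ignores level. In one simulated data set (n = 10, between-participant SD 10, error SD 4), r stayed at 0.608 when the mean change was set to 0, -3, -5, -10 and -20.

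**Reading 2: score against time (pre = 0, post = 1).** Now k = 2 and df = 10 × 1 - 1 = 9. With two occasions,

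r = t / √(t² + n - 1), where t is the paired t statistic.

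Check: t = -3.64 and n = 10 give -3.64 / √(13.25 + 9) = -0.77. In the same simulated data set:

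| Mean change | Paired t | r with time | Mixed-model time effect (SE) |
|---|---|---|---|
| 0 | 0 | 0 | 0 (1.81) |
| -3 | -1.656 | -0.483 | -3 (1.81) |
| -5 | -2.761 | -0.677 | -5 (1.81) |
| -10 | -5.521 | -0.879 | -10 (1.81) |
| -20 | -11.042 | -0.965 | -20 (1.81) |

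So r moves with the change, but it does not give its amount. Going from -10 to -20 points doubles the change and moves r only from -0.879 to -0.965. Conversely, one amount of change gives many values of r. For a mean fall of 5 points with n = 10, t = -5√10 / SD of change:

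- SD 3: t = -5.27, r = -5.27 / √(27.8 + 9) = -0.87
- SD 5: t = -3.16, r = -3.16 / √(10 + 9) = -0.73
- SD 10: t = -1.58, r = -1.58 / √(2.5 + 9) = -0.47

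**Reading 3: one measure against another.** With two occasions the coefficient reduces to Σ(dx·dy) / √(Σdx²·Σdy²), where dx and dy are each participant's changes, not centred on their means. Reversing the sign of every change in both measures leaves it the same, so improvement and worsening cannot be told apart. Because the changes are not centred, shared drift also enters. If individual changes are independent and each has a mean of m SDs of change, in opposite directions, the large-sample value is -m² / (m² + 1). Simulation at n = 10 agrees:

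| m | -m²/(m² + 1) | Simulated mean r | p < 0.05 |
|---|---|---|---|
| 1 | -0.50 | about -0.5 | 37% |
| 0.5 | -0.20 | -0.20 | 8% |
| 0.25 | -0.06 | -0.06 | 5% |

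With zero mean change, p < 0.05 occurred in 4.8%. The drift effect is large only if the mean change is large relative to its SD.

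**What the mixed model gives.** Its time effect is the mean paired difference in scale units (last column of the first table). At a mean change of -5, a 95% interval on 9 df is -5 ± 2.262 × 1.811, or -9.1 to -0.9.

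**Why the effect size needs a definition.** With equal SDs at both occasions and pre/post correlation ρ, an effect size on the SD of change is 1/√(2(1 - ρ)) times one on the between-participant SD. That ratio is 1.00, 1.29, 1.58 and 2.24 at ρ = 0.5, 0.7, 0.8 and 0.9.

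**The case against.** The strongest reply is that the next sentence already plans a mixed-model effect size for each measure. Under a heading about change with treatment, this is most naturally a pre/post effect. That stands: a reader might infer that aim (3) cannot be answered at all, and the document does not support that.

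A reader might also infer that the named correlation is blind to change. This is too strong. On the score-against-time reading it is a one-to-one transform of the paired t with the same p-value, so it detects change and its direction. What it lacks is the amount.

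Nor can it be said of the named method that a high coefficient would merely reflect stable differences between participants. That applies to an ordinary pre/post correlation; a repeated measures correlation removes those differences.

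Finally, the standardiser and model terms are detail that an article may leave to a full protocol or SAP, and this is a small descriptive pilot with no efficacy hypothesis. Both points are fair and limit the weight of the concern. They do not remove it, because the comparison method is stated, not omitted, and it does not match its stated purpose.

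**Conclusion.** The concern holds in a limited form. The comparison named for all six measures does not quantify change on any of the three readings, and the article does not say which is meant. The planned mixed model can supply the estimate, so aim (3) is recoverable, but that model is named only for an undefined effect size and not as the pre/post comparison. This should be fixed, but it does not threaten the study.

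The algebra (degrees of freedom, the link to the paired t, the uncentred changes) depends only on two occasions and, for the numbers, n = 10. The sizes of r, the percentages and the standardiser ratios rest on assumed SDs, mean changes and correlations, and say nothing about what this trial will observe.

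**What to change.** Replace the comparison sentence with wording such as:

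> For each of the six measures, the mean within-participant change (after the last treatment day minus day 1 before rTMS) will be estimated from the linear mixed model, with occasion as a fixed effect and participant as a random effect, and reported in raw units with a 95% CI. The effect size will be reported alongside, with its standardiser named.

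Drop the repeated measures correlation as the pre/post comparison, or keep it as a secondary description of association between measures, naming each pair. The choice of standardiser may sit in the SAP.

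The cost is a change of wording. The model is already planned, no new data are needed, and the article describes the study as ongoing.

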## Risks and Protection Against Risks

All of the parameters proposed for this study fall within the accepted parameters for safe rTMS administration with an estimated risk of <1 in 10,000 of inducing seizures in appropriately screened subjects (14–16). Overall, low frequency-rTMS protocols, such as the one used in this pilot study, are considered to be of minimal risk for serious adverse events and have been used extensively in previous research (20). LF-rTMS has been applied to over a hundred subjects with other cortical hyperexcitability syndromes (largely tinnitus and central pain) with no reports of seizures or other serious adverse events (21–23). A slight risk of headache and neck pain is expected, but these symptoms are typically self-resolving and/or treatable with over-the-counter analgesics. Other potential side effects include scalp discomfort at the site of stimulation, scalp or jaw or face tingling or muscle spasms, light headedness, and visual blurring.

To mitigate risks, all participants are screened prior to TMS (see exclusion criteria). Each participant is required to have a MRI scan performed within 3 years that does not show any concerning lesion. There have been reports of hearing loss with repeated TMS pulses, and thus all participants and investigators are required to wear ear plugs, consistent with what is worn during an MRI brain scan. An on-call neurologist is available at all times in the event of a seizure or other adverse study event. Study personnel involved in human subject interactions are BLS certified and specifically trained in seizure safety and what to do in the event of other medical emergencies. All adverse events are reported to the Colorado Multiple Institutional Review Board (COMIRB), and if a seizure were to occur, it would also be reported to the FDA. To monitor for adverse events, and make appropriate modifications, a side effects survey is given to each participant after each treatment session and at month one and month three after treatment is completed.

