## Introduction

People with Visual Snow (VS) syndrome perceive small, moving dots, which resemble the TV static of a poorly tuned analog television, in a constant manner throughout their visual field. Other symptoms include palinopsia or visual trails, light sensitivity, excessive awareness of flashes of lights and floaters, tinnitus, and balance problems. VS most often affects young people in the third decade of life, but it can strike anyone at any age, including children and older adults (1, 2). Comorbidity includes migraine headaches, which are present in 60–80% of people with VS (2). There is no effective treatment, and the cause is unknown. Many patients with VS have difficulty with visual functions and can struggle to continue working because of the visual symptoms associated with the syndrome (2). The International Headache Society (IHS) published criteria (3) for the VS syndrome and these criteria are summarized in Table 1.

**Table 1 T1:** Summary of international headache society criteria for visual snow (3).

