### Transcranial Magnetic Stimulation: Treatment Procedure

For treatment in this pilot study, bilateral low-frequency (1 Hz) repetitive transcranial magnetic stimulation (LF-rTMS) is administered to both right and left lingual gyri using a custom-built, 120°-angulated, 80 mm double figure-of-eight coil manufactured by Magstim Ltd (Whitland, Camarthenshire, UK). Targets are selected based on visual inspection of a participant's T1-weighted MRI images of the brain, and individual target coordinates are recorded in Montreal Neurological Institute (MNI) space. The TMS coil is positioned over the specified target location based upon the participant's MRI image in MNI space facilitated by the Brainsight™ interface, and LF-rTMS is administered at 110% of the phosphene threshold using the determined target and trajectory. Treatment sessions include two 15–20 min trains (one train per side) for a total of no more than 1,800 stimulations during each treatment session. Each session includes a total of 30–40 min of LF-rTMS stimulation time with a brief break in between sides. For each session, after treatment is complete, the participant is given a side effect survey. The rTMS treatment sessions occur daily for 5 days per week for two consecutive weeks.

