### Data Analysis

#### Side Effects

To determine whether any participant experiences untoward effects of TMS, a side effect survey is being used, as noted, and summary reports of adverse events will be published. It should be known that the cortical location of the treatment for this trial is different from previous studies, so it is possible to encounter side-effects not previously reported.

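### No pre-rTMS side-effect survey is stated, so in this uncontrolled study background headache could be recorded as an rTMS side effect and bias the aim 1 adverse-event summary upward

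*Protocol article*

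**What the plan says.** The article gives the timing of the side-effect survey in two places. Under Transcranial Magnetic Stimulation: Treatment Procedure: "For each session, after treatment is complete, the participant is given a side effect survey". Under Risks and Protection Against Risks: "a side effects survey is given to each participant after each treatment session and at month one and month three after treatment is completed". Both place it after rTMS.

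The survey's purpose is set out under Data Analysis, Side Effects: "To determine whether any participant experiences untoward effects of TMS, a side effect survey is being used". The same paragraph promises published summaries of adverse events and notes that the cortical target differs from that of earlier studies. The aims, stated after Table 1, begin: "Specifically, this study aims to determine: (1) adverse events and drop-out rate".

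On design, Methods and Analysis says: "The ongoing study is an open-label feasibility treatment study of VS utilizing a rTMS paradigm". No control group is described, and enrolment is capped at 10.

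On background symptoms, the Introduction says: "Comorbidity includes migraine headaches, which are present in 60–80% of people with VS". On expected effects, the Risks section says: "A slight risk of headache and neck pain is expected". It goes on to list scalp discomfort, tingling, muscle spasms, light-headedness and visual blurring.

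**The concern.** The survey is meant to show what TMS does to participants, which calls for a reference point. A control group would give one, and so would a rating from the same person before treatment. The article describes neither for this instrument.

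This matters most for headache. It is the first rTMS effect that the article names, it is common in the population being enrolled, and the exclusion criteria do not list migraine. A participant who arrives with a headache, or would have had one that day anyway, can report it on a post-session form. The form alone would not show whether it was there before the session.

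The adverse-event summary is one of the study's main products, and the article says that there are no published data on TMS in VS. An overstated headache proportion would therefore have no published figure in this population to be checked against.

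**Working it through.** **Is a pre-rTMS survey stated anywhere?**

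- Treatment Procedure: after each session.
- Risks and Protection Against Risks: after each session and at months 1 and 3.
- Methods and Analysis says in general terms that the assessments are given at baseline, but does not name this survey. The Abstract lists the pre- and post-treatment assessments: the CVSS, the VFQ-25, the GAD-7 and three visual tasks. The side-effect survey is not on the list.
- Performance of Outcome Measures gives the CVSS and the visual tasks twice before rTMS. The article thus does specify pre-treatment ratings where it plans them.

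The survey therefore has a stated schedule of 10 + 2 = 12 occasions, all after rTMS has begun.

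**Which expected effects overlap with background?**

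- Headache: direct overlap with migraine.
- Light-headedness and visual blurring: loose overlap. The Introduction lists balance problems and several visual symptoms of VS, but neither of these two by name.
- Scalp discomfort, tingling and muscle spasms: no overlap with the VS symptoms that the article lists.
- VS symptoms themselves: the CVSS gives two ratings before rTMS.

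**How large could the headache effect be?** The plan has no figure for adverse-event rates, so there is none to reproduce. Its precision figure for drop-out, the other half of aim 1, does not bear on this point.

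Inputs from the article: 10 participants, 10 sessions, migraine in 60–80%, so 10 × 0.6 = 6 to 10 × 0.8 = 8 participants with migraine.

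Assumptions not in the article: d headache days per month in those with migraine; independent days; a survey that records any headache that day; no headache caused by rTMS.

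The chance that a participant with migraine reports at least one headache over 10 session days is 1 − (1 − d/30)^10.

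| d (assumed) | Calculation | Chance | Of 6 to 8 with migraine |
|---|---|---|---|
| 1 | 1 − (29/30)^10 | 29% | 1.7 to 2.3 |
| 2 | 1 − (28/30)^10 | 50% | 3.0 to 4.0 |
| 4 | 1 − (26/30)^10 | 76% | 4.6 to 6.1 |
| 8 | 1 − (22/30)^10 | 96% | 5.7 to 7.6 |

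For d = 2 to 8 the range is 3.0 to 7.6, or about 3 to 8 of 10 participants. Over all 12 survey occasions the chances for d = 1, 2, 4 and 8 are 33%, 56%, 82% and 98%.

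These are counts of reports that could be misattributed. They do not estimate the bias in the published summary.

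**The case against.** The strongest reply is that the article never says how symptoms will be counted or attributed. A reader might infer that existing symptoms will certainly be tallied as rTMS side effects, but no passage supports that. The survey's items, recall period and wording are not shown. If it asks only for new or worsened symptoms, or only about the session itself, most background headache drops out. Headache history and rules for relatedness are also commonly left to a full protocol. This stands, and it makes the upward bias a possibility rather than a certainty.

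A second reply is that the overlap is narrow. A reader might extend the problem to VS symptoms in general. The article does not support this, given the CVSS baseline and the loose match with the other listed effects. This also stands.

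A third is that the illustration rests on assumed inputs. It does, and a session-specific question would cut the numbers sharply.

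A fourth is that post-session recording is enough for safety monitoring in a small open-label pilot, and that the randomized controlled trial it is meant to lead to would have its own comparison group. Both are fair. A reader might infer that the later trial would carry the bias forward in its own results, and that does not follow. What remains is this study's stated purpose of determining effects of TMS, for which monitoring alone gives no comparator.

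None of this removes the core of the point. The schedule is stated twice with no pre-treatment rating, and in this design a within-person comparison is the only one available. Even a new-or-worse question, if asked only after treatment, relies on the participant's recall of how things were before.

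**Conclusion.** The point holds as a risk of upward bias in one part of aim 1, chiefly for headache. It rests on the two stated survey schedules, the absence of a control group, the article's own migraine prevalence, and headache being an expected effect.

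Its size is not determined by the article. The figure of about 3 to 8 of 10 participants should be read only as the result of assuming 2 to 8 headache days per month, independent days, and a survey that records any headache that day. It is not a forecast of what the study will report. At 1 day per month it falls to about 2 of 10, and a survey limited to new or session-related symptoms would lower it further. No sample size, precision figure or efficacy analysis is affected.

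It is still worth acting on: the change is small, enrolment was continuing when the article was written, and a rating not taken before treatment cannot be recovered later.

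**What to change.** Give the same survey before session 1, ideally before each session. The visits at which the CVSS is completed before rTMS already offer a place for the first rating.

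Report symptoms that are new or worse than the pre-rTMS rating, with all-symptom counts alongside. Both are needed. From session 2 onward a pre-session rating may already contain a delayed effect of an earlier session, and the all-symptom count keeps that visible. At months 1 and 3, where there is no session, compare with the rating before session 1.

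If the form already asks only for new or worsened symptoms, or the full protocol has an attribution rule, say so in the report.

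The cost is a few minutes per visit on an existing form and a minor IRB amendment. The participant already treated will have no pre-session rating and should be reported with all-symptom counts only. Pre-session ratings will not identify an unrelated headache that starts during or after a session, so some background will remain.
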